## Abstract

**Background:**

Hematologic malignancies and their treatments are recognized for their significant long-term adverse effects on health-related quality of life. As a part of cancer treatment, physical exercise is known to improve physical functioning, but there are still questions regarding its impact on psychological and emotional functioning. Nonetheless, heart rate variability biofeedback (HRVB) is recognized for its positive effects on autonomic nervous system balance and emotional self-regulation. The Adapted Physical Activity and Cardiac Coherence in Hematologic Patients (APACCHE) protocol is a randomized, controlled superiority trial designed to evaluate the effects of HRBV training combined with an adaptive physical activity (APA) program compared to APA alone on the post-treatment quality of life of adult hematologic patients.

**Methods:**

Seventy patients aged 18–70 years, with various forms of hematological malignancies, in post-treatment remission within six months prior to beginning the study and who have been prescribed APA by a hematologist, will be randomly allocated in a 1:1 ratio to two 12-week treatment groups: HRVB + APA versus APA alone. APA sessions will consist of aerobic and resistance training for 1-h twice weekly. The HRVB training will consist of controlled breathing exercises with biofeedback of heart rate variability for 10 sessions and will include a daily home-based practice. The primary outcome will be to evaluate health-related quality of life (QLQ-C30, SF-36). The secondary outcomes will be to evaluate fatigue (MFI-20); anxiety and depression (HADS); clinical status with blood pressure, progression-free survival, overall survival, and body mass index; heart rate variability level and cardiac coherence score. All of these assessments will be evaluated initially (T1), 6 weeks after (T2), at the end of the 12 weeks (T3), and then at a 12-week post-intervention follow-up (T4).

**Discussion:**

To our knowledge, this is the first protocol to investigate the additional value of HRVB on physical exercise. In addition, there has been no study previously published about HRVB in hematologic patients. We hypothesize that overall quality of life and psychological and physical functioning will be improved, potentially offering a better understanding of supportive cancer care in hematology and inferring new perspectives in psychophysiological research in cancer.

**Trial registration:**

Current randomized controlled trial was registered 29 November 2017 on Clinical Trials.gov (NCT number: NCT03356171).

## Background

### Hematologic patients

Hematologic cancers are heterogeneous diseases, defined by hematopoietic myeloid or lymphoid cell tumors, originating from the bone marrow or the lymphatic system [1]. They include numerous different diagnostics, according to the 2008 World Health Organization classifications [2] and their revised criteria in 2016 [3], from indolent and chronic lymphoid tumors to rapidly aggressive acute leukemia. The prevalence of hematologic cancers has been constantly in progress in developed countries [4]. There were approximately 230,000 new cases of hematologic cancers in Europe in 2005 and patients with these types of tumors accounted for 7% of all cancer-related deaths in that same year [5].

Hematologic patients have poorer health-related quality of life [6, 7], with substantial changes in physical, psychological, and social components due to the disease and its treatments [8]. High-dose chemotherapy is often required, and sometimes hematopoietic stem cell transplantation (HSCT) is also administered. Serious physiological complications related to treatment side-effects have been reported such as cardiomyopathy [9], neuropathy [10], and decreased immune function induced by bone marrow damage related to the chemotherapy [11]. While most HSCT recipients regain functioning to carry out activities of daily living during the year following HSCT [6, 7], patients report persistent fatigue, anxiety, and depression at their one-year follow-up which affects their physical, emotional and social functioning [7]. Three years following treatment, patients were found to have higher fatigue, dyspnea and insomnia compared to the general population [6]. These symptoms are known to negatively affect physical and cognitive functioning and general quality of life [6]. Beyond residual symptoms, persistent psychological and social problems related to self-image, distress, isolation, and fear about the future or relapse are experienced by most patients undergoing HSCT [12].

This persistent symptomatology and their long-term negative effects on overall quality of life are a major concern for these hematologic patients [6–8]. Consequently, symptom management interventions should continue after treatment cessation to support the challenge of returning to an active daily life and to their former roles in work and society [12, 13].

### Complementary therapies to enhance health-related quality of life

#### Physical exercise

Regarding hematologic patients, programs based on endurance, resistance, relaxation or stretching are well tolerated [14], even by patients before, during or after undergoing HSCT [15]. Aerobic exercise, combined or not with resistance training, improves not only physical performances such as aerobic capacity, cardiovascular fitness and muscular strength, but also fatigue and overall survival [16, 17]. Furthermore, positive effects of physical exercise on immune function, with shorter duration of neutropenia and thrombocytopenia, were measured among patients undergoing HSCT [16]. Combining aerobic and resistance training, with moderate intensity (12–14 Borg scale, 70–80% max heart rate), up to 30 min and more, 3–5 times per week over 6–12 weeks, may be the most efficient for hematologic patients after HSCT [16].

Whereas physical exercise affects physical functioning and fatigue, there is no consensus about positive effects on psycho-emotional components of quality of life [15, 18, 19]. No conclusive results have been found regarding depression, anxiety, and sleep disturbance among hematologic patients [14], and no significant results were reported about the impact of a physical exercise program on improving social functioning for patients undergoing HSCT [15]. These results suggest that physical exercise alone may be limited to improve all components of quality of life and could therefore be combined with another intervention centered on psycho-emotional functioning to optimize its efficacy in cancer rehabilitation [20].

#### Heart rate variability biofeedback

Heart rate variability biofeedback (HRVB) is a behavioral intervention in order to improve the dynamic balance of the autonomic nervous system (ANS) and to regulate emotional state [21]. It consists of a regular breathing practice at a specific frequency of approximately 6 breaths/min that produces high amplitude of heart rate variability (HRV) [22].

HRV is defined by fluctuations in the inter-beat interval between all successive heartbeats, and is characterized with R-spikes spatial intervals of the ECG (RR intervals) in non-arythmic patients. HRV reflects the dynamic interaction between the sympathetic and parasympathetic nervous systems [23–25]. It is assessed in the time domain (e.g. standard deviation of normal-to-normal R-R interval (SDNN)) and in the frequency domain (e.g. fast Fourier transform (FFT)), providing information concerning the variability of RR intervals and the underlying nervous mechanisms [26]. HRV is recognized as a biomarker for good health: a high level (in a physiological range) of HRV indicates higher resilience and an ability to face challenges, such as stressors or exercise [27]; a reduced HRV measurement is associated with cardiovascular mortality and morbidity [28] or with serious psychological disorders, such as depression [29] and anxiety [30].

Two main autonomic nervous regulatory mechanisms are associated with HRV pattern: baroreflex and respiratory sinus arrhythmia [21]. The baroreflex maintains blood pressure (BP) by increasing HR if BP decreases and vice versa [31]. Respiratory sinus arrhythmia increases HR during inspiration and decreases it during expiration [32]. These oscillatory systems can synchronize themselves at a specific resonance frequency around 0.1 Hz with respiratory rate at approximately 6 breaths/min [22]. A specific HRV pattern known as cardiac coherence or psychophysiological coherence emerges from this synchronization and is characterized by a sine wave-like HRV pattern having a peak in the low frequency region centered around 0.1 Hz on the spectral analysis and a maximal amplitude in HRV signal [21, 33, 34].

HRVB positively impacts the cardiorespiratory system by improving HRV level, gas exchange and baroreflex gain [35]. On a broader scale, HRVB may improve the balance of the ANS and the regulation of inflammatory responses [36, 37]. HRVB could also be effective to promote psychological resiliency in terms of emotional responses and recovery from environmental stressors [34, 36, 38]. This research is supported by recent studies in functional neuro-imagery that have associated HRV with some areas of the limbic system and the prefrontal cortex which are both involved in emotional state regulation [38–40]. Several clinical studies concluded that patients with various chronic diseases responded well to HRVB, having reported satisfaction and positive well-being after biofeedback practice [37, 41, 42]. Their results are promising for clinical outcomes revealing positive effects on physiological and psychological symptomatology. In addition, most of these studies determined the feasibility of HRVB and the achievement of cardiac coherence state by patients [37, 41, 42].

### Objectives and outcomes

Our protocol evaluates the superiority of an adapted physical activity (APA) program combined with HRVB (experimental group), over a program with APA only (control group). The APA program is suggested for hematologic patients as a supportive cancer care by the ACSM exercise guidelines for cancer survivors [14] and has also been recommended specifically for patients undergoing HSCT [16].

The primary objective will be to investigate the effects of a 12-week intervention of HRVB associated with an APA program versus APA only on overall quality of life measured with Quality of Life Core Questionnaire (QLQ-C30) in hematologic patients. Specifically, we will evaluate the effects on fatigue, anxiety and depression; assess clinical status with BP, progression-free survival, overall survival, and body mass index (BMI); and measure HRV level, cardiac coherence score, physical condition, satisfaction, and adherence to the protocol (to ensure the quality of support provided to patients).

### Hypothesis

Patients who participate in HRVB training in addition to an APA program versus APA only are expected to:
Improve their overall quality of life and reduce their overall fatigue, anxiety and depression.Improve their clinical status through BP, progression-free survival, overall survival, and BMI.Increase their HRV level and cardiac coherence score.

## Methods/design

### Design and setting

The APACCHE protocol is a single-centre, parallel, randomized controlled superiority trial in adult hematologic patients who have been treated for hematologic malignancy in the hematology unit of the Hospital of Reunion Island, France. Modifications of this current protocol will have to be written as a protocol amendment by the Methodology and Data Management Centre and will have to be validated by the French ethical committee.

### Study population

#### Inclusion criteria

Our study will include French-speaking patients, aged 18–70, with various forms of hematological malignancies, in post-treatment remission (full or partial) within the 6 months prior to the study, with stable hemoglobin levels (≥9 g/dl) and for whom APA is recommended by a hematologist. All patients will give their written informed consent.

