**Fig. 2 Fig2:**
[figure not shown]
Timeline of the APACCHE study

At T0, hematologists will deliver a brochure about the APA program and a briefing note regarding the protocol to potential participants. They will complete a dedicated form related to the medical prescription of the APA program including details about clinical status and specific recommendations for the APA instructor. Then, the APA instructor will contact interested patients to make a first appointment (T1).

At T1, the hematologist will obtain informed consent from the patients, and will proceed to the randomization. For study participants who will be included in the experimental group, a clear description about HRVB training will be given by the APA instructor.

At T1, T2, T3 and T4, quality of life, fatigue, anxiety and depression will be assessed by trained interviewers. Clinical status will be collected by the hematologist and HRV level, cardiac coherence score, and GPAQ will be measured by the APA instructor. Physical tests will be conducted only at T1, T2 and T3. (Table 1).

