#### Blinding and intervention assignment

The specificity of the HRVB and APA interventions will not allow for the use of double-blind assignments for the APA instructor and hematologists. However, we will establish a blinding on the questionnaire assessments for the trained interviewers to maintain a high level of evidence.

Randomization will be balanced in both groups, with a 1:1 allocation ratio, without stratification. The randomization list will be established by the statistician from the Methodology and Data Management Centre before the start of the research. Different sizes of randomization blocks will be used to leave the investigators blind to their size and to avoid predictable allocation. Randomized block sizes of 4,6,8 or 10 blocks will be performed on STATA®. The randomization list will then be imported into the CsRandom module of the Ennov Clinical® electronic case report form (eCRF), which the investigator will use to perform the randomization.

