#### Statistical analysis

To evaluate effectiveness of HRVB, we will compare the average evolutions (T3-T1 difference score) between the experimental group (HRVB+APA) and the control group (APA). Student’s t-test will be performed for the different dimensions and scale sub-scores of each questionnaire, as well as cardiac coherence score and SDNN. An analysis of longitudinal data collected at T1, T2, T3 and T4 will be conducted using a linear mixed model with structured covariance residuals. The bivariate survival analysis (death and / or relapse, survival without serious infectious events) will be carried out using the Kaplan-Meier method. Group comparison will be calculated using the log-rank test.

All hypotheses will be tested in a single analysis, intention to treat (according to the group assigned by the randomization), bilaterally at the threshold α = 5%. The analyses will be performed with SAS® (version 9.4, SAS Institute Inc., Cary, NC, USA). At the end of the research study, investigators will anonymize the collected data and results will be submitted to the research partners. The statistician, methodologist and investigators will have access to the final dataset. An article in a journal indexed on Medline will be carried out in post-trial.

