## Discussion

Previous studies have investigated the effectiveness of HRVB compared to physical exercise [67–69]. To the best of our knowledge, there have been no studies about the added value of HRVB on physical exercise to enhance overall quality of life. While recent studies about HRVB training have demonstrated the feasibility and the effectiveness of HRVB in chronic patients [37, 41, 42], it has not yet been done in cancer patients, namely in hematology. Most clinical studies conclude that HRVB can reduce symptomatology of chronic disease and improve HRV level, supporting our hypothesis that HRVB may be feasible and effective in recovery of hematologic patients.

We hypothesize that HRVB associated with an APA program will be more effective than an APA-only program in improving quality of life during post-treatment in adult hematologic patients and expect the following outcomes from this experimental group: i) significant improvements in overall quality of life and a reported decrease in overall fatigue, anxiety and depression; ii) increased HRV levels, reflecting a better physiological regulation through autonomic control of the heart; iii) better BMI and BP measurements; and iv) less infectious events, relapses and deaths. All of these variables should be improved between T1 and T3. The results recorded at T3 could be sustained through T4, especially if patients are persistent with their home-based practice for both cardiac coherence and physical exercise.

All participating patients will be in remission for hematologic malignancies that have required hospitalization, caused sudden disruptions to their day-to-day lives, and/or have required particular aggressive treatments with high-dose chemotherapy, affecting patients’ overall quality of life. To avoid age-related effects, we have chosen a within-subject design and will exclude patients over 70 years.

Our short-term HRV recording protocol is based on the recommendations from Task Force [70] and more recently from Laborde [57], who has suggested guidelines for psychophysiological research. Although electrocardiogram is more accurate, we use the pulse sensor to assess pulse-to-pulse interval data which accurately approximates the inter-beat interval [71]. To analyze HRV data in time-domain and frequency domain, *HRVanalysis* will be used [58].

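### The effectiveness test takes no account of transplant history or time since treatment: it is valid, but it forgoes cheap precision and leaves the single realised estimate open to chance imbalance

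*Protocol article*

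**What the plan says.** Inclusion criteria (protocol article) admits patients "with various forms of hematological malignancies, in post-treatment remission (full or partial) within the 6 months prior to the study". Neither that section nor Exclusion criteria mentions transplant, so patients with and without one can enter.

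The background section Hematologic patients describes diagnoses "from indolent and chronic lymphoid tumors to rapidly aggressive acute leukemia", notes that "sometimes hematopoietic stem cell transplantation (HSCT) is also administered", and reports that "most HSCT recipients regain functioning to carry out activities of daily living during the year following HSCT". The Discussion describes the malignancies of participating patients as ones that have required hospitalisation, disrupted daily life, "and/or have required particular aggressive treatments with high-dose chemotherapy", so treatment intensity is mixed.

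Blinding and intervention assignment states: "Randomization will be balanced in both groups, with a 1:1 allocation ratio, without stratification". The varying block sizes (4, 6, 8 or 10) balance arm sizes only.

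Statistical analysis fixes the effectiveness comparison: "we will compare the average evolutions (T3-T1 difference score) between the experimental group (HRVB+APA) and the control group (APA", using Student's t-test. A linear mixed model on T1 to T4 is also planned; the article names no prognostic covariates for it.

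At T0 the hematologists fill in the prescription form: "They will complete a dedicated form related to the medical prescription of the APA program including details about clinical status".

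**The concern.** The outcome is change over 12 weeks. For a recently transplanted patient, that window lies inside the recovery year that the background describes. A patient treated one month ago and one treated six months ago may be expected to change by different amounts even with the same T1 score. A change score removes differences in starting level, not in rate of recovery, and adjusting for T1 alone would not fully remove them either.

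The t-test leaves any such differences in the error term. With 35 patients per arm, one allocation can also put noticeably more transplanted or recently treated patients in one arm. At stake is the precision of the HRVB estimate in a trial planned at only 80% power, and how credible that estimate looks if the baseline table turns out uneven.

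**Working it through.** **1. The plan's own sample size.** From Sample size: difference 5, SD 7, power 80%, 10% missing or dropout. Two-sided alpha 5% is from Statistical analysis.

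n per arm = 2 × (1.960 + 0.842)² × 7² / 5² = 30.8, so 31. Then 31 / 0.9 = 34.4, so 35 per arm and 70 in total. The stated figure reproduces. (The t-distribution version gives 32 per arm, 36 after inflation, 72 in total.)

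**2. The unadjusted test as planned.** Evaluable patients: 70 × 0.9 = 63, taken as 32 and 31. If 7 is the total SD of change, the standard error is 7 × √(1/32 + 1/31) = 1.76 points, and noncentral-t power for a difference of 5 is 79.7%. On this reading nothing is lost against the plan's promise.

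**3. What two covariates could add.** The documents give no transplant share, recovery gap or time slope, so these are assumptions: 40% transplanted (variance 0.4 × 0.6 = 0.24); months since treatment uniform over 0 to 6 (variance 6²/12 = 3); the two factors independent; gap D between transplanted and other patients in natural 12-week change; slope s in points per month.

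R² = (0.24 D² + 3 s²) / 49; residual SD = 7 √(1 − R²); two degrees of freedom removed.

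| D | s | R² | residual SD | power |
|---|---|---|---|---|
| 3 | 0.5 | 2.91/49 = 0.06 | 6.79 | 82.0% |
| 5 | 1 | 9.00/49 = 0.18 | 6.32 | 87.0% |
| 8 | 1 | 18.36/49 = 0.37 | 5.54 | 94.1% |

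This ignores the small cost of adjusting for covariates that are not exactly balanced between arms, so the low-end gain is at most about 2 percentage points.

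**4. Chance imbalance in one allocation.** Two independent binomials, 35 per arm. A difference of 6 or more transplanted patients (6/35 = 17 percentage points) has probability 17.9% at a 40% share, and 15.1% to 18.8% for shares of 30% to 50%. A difference of 7 or more at 40% has probability 11.2%. A 6-patient difference shifts the estimate by (6/35) × D: 0.9 points at D = 5 and 1.4 at D = 8, against a target of 5. That is 0.5 to 0.8 of the 1.76-point standard error.

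**5. If 7 is instead the SD within recovery groups.** Sample size does not say which SD it is. With half the patients transplanted and 32 per arm:

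- D = 5: total SD = √(49 + 0.25 × 25) = 7.43; unadjusted power 75.5%.
- D = 10: total SD = √(49 + 0.25 × 100) = 8.60; unadjusted power 62.9%.

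In 20,000 simulated trials for each setting, the adjusted model had power 80.1% and 79.7% respectively.

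**6. Validity.** In the same simulations the unadjusted mean estimate was 0.00 to 0.02 under no effect and 5.02 to 5.03 under a true effect of 5. The unadjusted type I error was 4.8%.

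**The case against.** Unstratified blocked randomisation with broad eligibility and an unadjusted test is a legitimate design for a 70-patient single-centre trial, and nothing in the article contradicts it. Four stronger readings are tempting and do not hold.

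- **That the contrast is biased.** It is not. Randomisation makes it unbiased over allocations, and the t-test's standard error already covers chance imbalance. The illustrated shift is under one standard error and is as likely to work against HRVB as for it.
- **That the trial is underpowered for this reason.** If 7 is the total SD of change, recovery differences are already inside it and power is about 80%. The shortfall in step 5 needs the other reading of the SD, which the article does not establish.
- **That the documents show unequal recovery by transplant status.** They give no comparison with non-transplanted patients and no 12-week QLQ-C30 change. The same sentence on regained functioning also reports persistent fatigue, anxiety and depression at one year. Pooling by transplant is inferred from the eligibility sections' silence, and the six-month limit could refer to when remission was reached rather than to when treatment ended.
- **That mixing full and partial remission is itself a fault.** Nothing in the documents says how recovery differs between the two, and no calculation here rests on it.

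It can also be said that covariates are often listed in an unseen full protocol or SAP, and that the mixed model might contain them. That stands for the mixed model. It does not dispose of the T3-T1 comparison, because a t-test is a named method that takes no covariates.

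**Conclusion.** The point holds as a matter of precision, not of validity. The plan names an unadjusted test for a 12-week change in patients whose natural recovery, on the article's own background, plausibly varies with transplant history and time since treatment. Adjusting for both would raise power from about 80% to between 82% and 94%, if they explain 6% to 37% of the variance of change and 7 is the total SD. The upper end needs a natural-recovery gap of 8 points, larger than the 5-point target effect; at the lower end the gain is about 2 percentage points. If 7 is a within-group SD, adjustment would instead restore roughly the planned 80%. The documents do not say which case applies, but in neither would the adjustment cost much.

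**What to change.** In Statistical analysis, replace the t-test on T3-T1 with a linear model containing treatment group, prior transplant (yes/no) and months since end of treatment, both prespecified as baseline covariates. Put the same two covariates, with their interactions with time, in the linear mixed model; main effects alone would not capture different rates of change. Record both in the eCRF at T1, and make the change before any comparative results are seen, since later adjustment would look selective.

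The cost is two degrees of freedom and two eCRF fields, with no extra patients or visits. Time since treatment is close to what staff must establish for eligibility, and clinical status is already documented at T0. Stratifying the randomisation by prior transplant is an option if the list is not yet in use, but the fix does not depend on it.
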